## Abstract

**Background:**

Medication errors are a leading cause of mortality and morbidity. Clinical pharmacy services provided in hospital can reduce medication errors and medication related harm. However, few rural or remote hospitals in Australia have a clinical pharmacy service. This study will evaluate a virtual clinical pharmacy service (VCPS) provided via telehealth to eight rural and remote hospitals in NSW, Australia.

**Methods:**

A stepped wedge cluster randomised trial design will use routinely collected data from patients’ electronic medical records (*n* = 2080) to evaluate the VCPS at eight facilities. The sequence of steps is randomised, allowing for control of potential confounding temporal trends. Primary outcomes are number of medication reconciliations completed on admission and discharge. Secondary outcomes are length of stay, falls and 28 day readmissions. A cost-effectiveness analysis (CEA) and cost-benefit analysis (CBA) will be conducted. The CEA will answer the question of whether the VCPS is more cost-effective compared to treatment as usual; the CBA will consider the rate of return on investing in the VCPS. A patient experience measure (*n* = 500) and medication adherence questionnaire (*n* = 100 pre and post) will also be used to identify patient responses to the virtual service. Focus groups will investigate implementation from hospital staff perspectives at each site.

Analyses of routine data will comprise generalised linear mixed models. Descriptive statistical analysis will summarise patient experience responses. Differences in medication adherence will be compared using linear regression models. Thematic analysis of focus groups will identify barriers and facilitators to VCPS implementation.

**Discussion:**

We aim to demonstrate the effectiveness of virtual pharmacy interventions for rural populations, and inform best practice for using virtual healthcare to improve access to pharmacy services. It is widely recognised that clinical pharmacists are best placed to reduce medication errors. However, pharmacy services are limited in rural and remote hospitals. This project will provide evidence about ways in which the benefits of hospital pharmacists can be maximised utilising telehealth technology. If successful, this project can provide a model for pharmacy delivery in rural and remote locations.

**Trial registration:**

Australian New Zealand Clinical Trials Registry (ANZCTR) -ACTRN12619001757101 Prospectively registered on 11 December 2019. Record available from: https://www.anzctr.org.au/Trial/Registration/TrialReview.aspx?id=378878&isReview=true

## Background

Globally, medication errors are a leading cause of avoidable morbidity and mortality with an estimated cost of $42 billion annually [1]. Hospital pharmacists play a key role in reducing medication errors through medication reconciliation [2–5]. Medication reconciliation (Med Rec) is the process of ensuring that patients receive prescribed medicines and that accurate, current and comprehensive medicines information follows them at all transfers of care. In hospitals, Med Rec has been reliably found to improve medication safety [6–11] and has been identified as an international priority by the World Health Organization [2, 6, 12].

In Australia medication safety is addressed through Standard 4 of the National Safety & Quality Health Service Standards (NSQHS) which includes safe prescribing, dispensing, administering and monitoring of appropriate medicines to informed patients [13]. However, medication-related incidents are the second most frequently reported incidents in NSW hospitals [14]. Consequently, improved medication management is a high priority, particularly in rural and remote settings where clinical pharmacy services are limited.

Australian research indicates that patients’ problems understanding and using their medications increases the risk of readmission 2.3 times [8, 15]. Integrating clinical pharmacists into hospital settings improves medication management, reduces medication harm, supports patients and decreases unwarranted clinical variation [16]. However, there is limited provision of Med Rec in rural Australian hospitals due to few on-site pharmacists [17–20] consequently patients are at a higher risk for medication-related harms [21]. Virtual or telehealth pharmacy services are one option to address the lack of on-site pharmacists.

Virtual pharmacy services have been implemented across parts of rural and remote Australia, particularly Queensland, however much of the literature reports on outpatient medication reviews rather than inpatient services [16, 22–24]. A feasibility study evaluating a service providing virtual clinical pharmacy reviews for inpatients in rural and remote regions was found to be acceptable [23]. Despite this, few studies have since reviewed service efficacy, with most studies focussing on patient satisfaction [23]. The use of virtual service delivery has been demonstrated to increase accessibility to specialist care particularly for rural and remote populations including Aboriginal communities, with evidence supporting the use of virtual technologies for the management of chronic diseases [25].

Three small studies have assessed the feasibility and acceptability of virtual pharmacy services in rural and remote locations [16, 23, 24]. This study will add to existing literature to provide evidence about the feasibility and efficacy of virtual pharmacy services in relation to patient outcomes, patient experience and economic factors.

The VCPS evaluation aims to 1.) Investigate if the VCPS results in a detection of preventable medication harms, reductions of readmission, falls and length of stay; 2.) Identify if the VCPS is cost-effective; and 3.) Assess if the VCPS is perceived to be an acceptable service for patients and clinicians.

Western NSW Local Health District (WNSWLHD) and Far West Local Health District (FWLHD) comprise some of the most remote regions in NSW, Australia. The two districts cover almost 450,000km^2^ with a population of 300,000 people. Services are provided by a combination of rural referral hospitals, rural hospitals, multipurpose facilities and nurse-only remote clinics. Onsite clinical pharmacy services are provided to only seven of thirty eight facilities, resulting in noncompliance with Standard 4 of the National Safety & Quality Health Service Standards (NSQHS) [13]. Existing telehealth infrastructure along with recent roll out of electronic medication management (eMeds) in the electronic medical record (eMR), has provided the infrastructure for a virtual clinical pharmacy service (VCPS).

## Methods/design

The VCPS evaluation will employ a stepped wedge cluster randomised trial design, where the intervention is sequentially implemented at eight facilities. The ‘steps’ are the order in which these sites cross-over from the control condition (pre-VCPS) to the intervention condition (VCPS). The sequence of the steps is randomised, allowing for control of potential confounding temporal trends. The cross-over will occur across 8 waves or steps (one site per step), each 1 month apart with a 2 month ‘in-transition’ period (see Fig. 1).

**Fig. 1 Fig1:**
[figure not shown]
VCPS stepped wedge cluster randomised control trial design. There are a total of 8 steps, with each step being one month apart. The light blue represent sites unexposed to the intervention (control). White represents sites where the service is being introduced and no data will be used in the analysis. Dark blue represents sites exposed to the VCPS, and purple the service continuation and evaluation

The virtual pharmacy service will be delivered in six rural NSW hospitals that do not have an on-site pharmacist but are using electronic medication management and patient record systems and have more than twenty inpatient admissions per month; and two remote hospitals that have between seven and thirteen admissions per month and fit the other inclusion criteria. All adult patients of emergency departments and inpatient wards of the participating hospitals will be included in the study. The order of the site implementation will be determined by computer-generated random numbers.

The intervention will consist of utilising the eMR, eMeds and a wireless teleconferencing cart with two–way audio and visual called a ‘Wallie’ to provide clinical pharmacy services to study sites. Virtual Pharmacists will work 8.30 am to 4.30 pm, Monday-Friday of each week over the study period where it is anticipated they will see up to ten patients per pharmacist per day.

Virtual clinical pharmacists will conduct Med Rec on admission, discharge or transfer and document a medication history in eMeds. A summary of the Med Rec and any identified issues will be documented on the eMR Medication Management Plan. To ensure continuity of medication management on discharge back to the community, the pharmacist will provide an updated medication list on discharge. The virtual pharmacist will provide comprehensive information to the patient or carer to enable safe and effective use of the medications. This will be tailored to suit the patient’s individual circumstances and may be in the form of verbal instructions, demonstration, education, a medication list, written advice or a consumer medicines information sheet. Pharmacists will also undertake clinical medication review for inpatients of the facilities and provide medication advice to Doctors and Nurses. Any harms or clinical incidents arising from the VCPS will be addressed using the NSW Health Incident Management System (IMS) and investigations will be conducted according to clinical governance processes.

Routinely collected, de-identified health data will be analysed pre and post VCPS (see Table 1). Data will be collected from the electronic medical record and Health Intelligence Unit (HIU) reports. A waiver of consent has been granted for this de-identified data. Patients receiving the service will be invited by nursing staff at their facility to complete a patient experience measure and a medication non-adherence questionnaire [26]. Staff at participating hospitals will be invited by email from the research team to a focus group about their experience of the virtual pharmacy service. Participation will be voluntary and written consent required.

**Table 1 Tab1:** Measures and routinely collected data source for VCPS evaluation

Outcome Measure	Data Source	Level of Data
% medication reconciliation on admission	eMR Report EM002	Facility
% medication reconciliation on discharge	eMR Report EM002	Facility
VTE Prophylaxis rates	Audit Office report	Facility
Antimicrobial usage	iPharmacy Dispensing Software	Facility
% medication list on discharge	Custom eMR report	Patient
28 day readmission	HIU report	Facility
28 day readmission Aboriginal patients	HIU report	Facility
Length of stay	HIU report	Facility
Length of stay Aboriginal patients	HIU report	Facility
Falls	HIU report	Facility
Detection of preventable medication errors	HIU report	Facility
Economic analysis (cost effectiveness) & scalability	HIU reports	Facility
**Process Measure**	**Data Source**	**Level of Data**
Number of medication reconciliation completed	eMR report EM002	Facility
Number of medication lists on discharge	Custom eMR report	Patient
Number of referrals/ number of referrals completed	eMR report PC011	Patient
Pharmacist Interventions	eMR DA2 Clinical Pharmacy Interventions	Patient
Time taken to undertake interventions	eMR DA2 Clinical Pharmacy Interventions	Patient
Time taken to provide education	eMR DA2 Clinical Pharmacy Interventions	Patient
Number of consultations	eMR report PC011	Patient
Uptake of pharmacy recommendations	eMR DA2 Clinical Pharmacy Interventions	Patient
Number of pharmacist AMS reviews	eMR report PC011/ eMR Report EM008	Patient

The primary outcome variables are: 1) the proportion of separations (“discharged home by the hospital”) where the medication reconciliation occurred on admission; and 2) the proportion of separations (“discharged home by the hospital”) where the medication reconciliation occurred on discharge. Secondary outcome variables include 28-day readmission, hospital length of stay (LOS), number of falls and detection of medication-related errors. Our analyses will comprise generalised linear mixed models, with fixed effects for time, period (pre vs post), and patient-level confounding variables, as well as random effects for facility and patient to model clustering/repeat measures. Analyses will exclude separations where the patient is transferred to another facility.

Sample size: Across the eight sites a referral rate of 29 patients per month is estimated yielding approximately 2088 patients over the intervention period. Assuming a baseline medication reconciliation rate on admission of 11% (a similar rate for discharge medication reconciliations), an intra-class correlation of 0.05, and an average of 29 patient separations per site per month,) there will be over 90% power to detect an absolute 10% increase in the proportion of reconciliations performed on admission and discharge, with a type 1 error rate of 2.5%.

A PREMS will be conducted with patients who have seen the virtual pharmacist. The PREM survey consists of 10 questions which will be delivered while the patient is in hospital using a tablet device and the Customer Feedback Solutions electronic system. The PREMS will be delivered electronically via Customer Feedback Systems (CFS). CFS will securely store the results and provide de-identified reports monthly.

The PREMS will be used to quantitatively assess improvements in patients’ knowledge and perceived acceptability of virtual pharmacy. The VCPS questions address patient communication of medication management during hospital admission, patient’s confidence managing medications and overall satisfaction with the VCPS.

To evaluate the acceptability of VCPS against face to face pharmacy services, PREMS will be conducted on the general medical wards at two hospitals with patients who have seen a face to face inpatient pharmacist. The general medical ward was chosen as it will have the most similar patient population to the study sites. Data will be collected from the comparison sites between May 2020 and June 2021.

All inpatients receiving the VCPS will be invited to complete the PREMS (estimated *n* = 500). All inpatients receiving an inpatient face to face pharmacy service on the medical wards at two comparison hospitals within a 3 month time period (to be negotiated with the sites) between March 2020 and June 2021 will be asked to complete the PREMS (estimated *n* = 500). A sample of this size will allow detection of differences in responses between demographic sub-groups of at least 0.3 standard deviations (i.e. a moderate effect size), with 90% power and 5% type 1 error rate. Descriptive statistical analysis will summarise patient answers, and linear regression models will be used to explore characteristics associated with the overall score using age, sex and Aboriginality as independent variables.

Medication adherence refers to whether a patient takes their medications as prescribed and is a primary determinant of treatment success. Poor adherence to medications is common in patients with chronic disease and in patients prescribed preventative medications. The 26 question Voil’s Medication non-adherence questionnaire (Voil’s) is validated to identify non-adherence behaviour in a number of chronic disease populations and scores have been show to correlate well with objective measures and clinical outcomes [26]. The measure records reasons for nonadherence. This is important in a rural and remote setting where availability of medication may be limited or the cost prohibitive. Identifying the reasons for non-adherence allows interventions to be tailored to those.

The Voil’s will be administered to patients on admission to study sites in both control and intervention periods electronically via Customer Feedback Systems (CFS). CFS will securely store the results and provide de-identified reports monthly. The Voil’s will then be repeated 4 weeks post discharge to assess changes in medication adherence due to the VCPS. A follow-up survey will be administered via text message invitation requesting the patient complete the questionnaire electronically via the Customer Feedback Systems platform. A sample of 75 patients in the pre period and 75 patients in the post period (across all sites) will give the study 85% power to detect an increase in adherence of 0.5 standard deviations (a moderate effect size), with a type 1 error rate of 5%.

A list of eligible patients that are admitted will be used as a sampling frame, and patients will be randomly selected from this frame using a computerised program, and approached to complete the Voil’s. A participation consent form is available from the corresponding author.

Characteristics of patients responding in pre and post collection periods will be compared using independent sample t-tests (for continuous variables) or chi-square tests (for categorical variables). Differences in adherence between patients in the pre period and patients in the post period will be compared using linear regression models, adjusting for patient characteristics that may have changed between the periods.

An economic analysis will consist of a cost-effectiveness analysis (CEA) and cost-benefit analysis (CBA) [27, 28]. These analyses will be conducted in accordance with international best-practice for such analyses in health care including: adoption a health sector perspective; transparent and scientific methods to identify, measure and value both costs and outcomes; modelling and uncertainty testing of input parameters; and, interpretation of results within a broader decision-making framework. The CEA will answer the question of whether the VCPS is more cost-effective than compared to treatment as usual; the CBA will consider the rate of return on investing in the VCPS. Both analyses will rely on health care utilisation data outlined in Table 1 that identifies and measures resource use associated with the VCPS including: additional pharmacist time to deliver the intervention; patient and clinician education; and, any system level changes that have occurred to facilitate the implementation of the intervention. Resource use will be collected by the virtual clinical pharmacist and stored in the patient’s clinical record on the eMR as in standard clinical practice. Change in 28 day re-admission will be used as the primary outcome in the CEA. The CBA will attempt to quantify a wider range of outcomes associated with the VCPS that can be valued in monetary terms such as LOS, the cost of treating adverse events (falls, medication-related errors) and potentially preventable admissions. Monte Carlo analysis will be used to derive 95% uncertainty intervals for costs and outcome with results presented in a scatterplot (i.e. cost-effectiveness plane). The results of the CEA will be considered in the context of other decision-making criteria such as: capacity of the intervention to reduce inequity; acceptability to stakeholders; feasibility; sustainability; and, potential for other consequences. Results of the CBA will be expressed as a ratio of benefits to costs whereby a benefit cost ratio > 1, suggests that the VCPS is a good return on investment.

A staff focus group will be held at each participating site 3 months after the beginning of the VCPS transition period. The focus group will investigate the perceived acceptability of the service for staff. All staff who work in clinical areas where the VCPS operates will be asked to participate in the focus group. Senior staff and managers’ will participate in a separate focus group to all other staff to take into account potential power relationships that may inhibit the responses of junior staff. The focus group will be held 3 months after the VCPS commences to provide adequate time for staff to be exposed to the service. The focus group discussion will explore the issues, benefits, barriers and overall acceptability of the VCPS. A participation consent form is available from the corresponding author.

A qualitative approach will be used to undertake focus groups with participating staff (*n* = 25). The focus groups will investigate implementation processes and those affected by them to understand the context of VCPS implementation [29, 30]. The focus groups will be audio-recorded, transcribed verbatim and entered into QSR NVivo. Thematic analysis will be utilised to deductively and inductively identify barriers and facilitators to the VCPS implementation. Data files and transcripts will be stored on a password protected server only accessible by the research team.

There was no patient or public involvement in the research design. Community consultation with Australian Indigenous communities in the study sites will be conducted prior to the VCPS implementation to explain the project and identify and respond to any concerns. Indigenous Australian comprise up to 60 % of the population in some sites. If community Elders do not support the pharmacy service, or the study, Indigenous people will not be included in the data collection. Indigenous research team members will conduct the consultations.

Data monitoring committee: A data monitoring committee has not been formed because there are minimal risks associated with the study. However, a project governance group has been formed that includes academic and research pharmacists, government clinical practice and telehealth specialists and local health executives. This group will meet quarterly and will be responsible for monitoring the project progress and addressing any problems that arise.

The study results will be communicated to the funding body in regular reports. The research team will also seek to publish the results in peer reviewed journals, and in newsletters and research snapshots back to the hospital sites and surrounding communities where the trial took place. There are no restrictions on publication. Authorship eligibility will follow the International Committee of Medical Journal Editors (ICMJE) guidelines. There are no plans to grant public access to the participant level dataset. The full protocol is available from ANZCTR.

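### The site order is described only as random, with no restriction to keep the two much smaller remote hospitals off the first and last steps; a near-costless restriction would remove the least precise orders

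*Protocol article*

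**What the plan says.** All of this is in the Methods/design section of the protocol article.

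- **Sites.** Six rural hospitals qualify with more than twenty inpatient admissions a month. They are joined by "two remote hospitals that have between seven and thirteen admissions per month and fit the other inclusion criteria".
- **Order.** The same paragraph, after the Fig. 1 caption, gives the allocation method in one sentence: "The order of the site implementation will be determined by computer-generated random numbers". No stratification, constraint or size balancing is mentioned.
- **Layout.** One site crosses over at each of eight monthly steps. Each site has a 2-month transition, and the Fig. 1 caption says that no data from it are used.
- **Planning figures.** The sample size paragraph assumes "an average of 29 patient separations per site per month", makes no allowance for unequal sites, and concludes that "there will be over 90% power to detect an absolute 10% increase in the proportion of reconciliations performed on admission and discharge".

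**The concern.** The difference in site size is known before randomisation. If 29 is the per-site mean, the monthly total is 8 × 29 = 232. With remote sites at 13, 10 or 7 a month, the six rural sites must then average 34.3, 35.3 or 36.3, which is roughly three to five times as many.

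In a stepped wedge with one site per step, the sites do not carry equal information. The first site to cross over supplies most of the early exposed data, and the last supplies most of the late control data. With the transition months removed, few site-months remain for comparing exposed with unexposed care near the two ends. A small hospital at an end therefore costs more precision than one in the middle. What is at stake is avoidable loss of precision in a trial with only eight clusters, not bias.

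**Working it through.** **Inputs from the article:** 8 sites and 8 steps, one site per step; 2 transition months excluded per site; 29 separations per site per month; 2088 patients; baseline 11%; absolute increase of 10 points; ICC 0.05; type 1 error 2.5%.

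**Assumptions of mine:** two-sided alpha; 11 calendar months, so that the site at step k has k control months, 2 excluded months and 9 − k exposed months; month as a categorical effect; remote sites at 10 a month (range 7 to 13) and rural sites at (232 − 20)/6 = 35.3. The layout agrees with the planned total: 8 sites × 9 analysed months = 72 site-months, and 72 × 29 = 2088.

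**Method.** Hussey–Hughes generalised least squares variance with a random site intercept and fixed time effects.
- Total variance: (0.11 × 0.89 + 0.21 × 0.79)/2 = 0.1319. Of this, 5% is between sites.
- Power = Φ(0.10/√Var − 2.241), where 2.241 is the two-sided 2.5% critical value.

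**The plan's own figure first (equal sites of 29).**
- 9 months, no transition gap: Var = 0.000703, so 0.10/0.02651 − 2.241 = 1.53 and power is 93.7%. This agrees with the stated figure.
- 11 months, transition excluded: Var = 0.001196, so 0.10/0.03458 − 2.241 = 0.65 and power is 74.2%.

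**Placing the two small sites.** There are C(8,2) = 28 placements. A remote site is at step 1 or 8 in 28 − C(6,2) = 28 − 15 = 13 of them (46%). Results for the transition-excluded layout, remote sites at 10 a month:

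| Placement of the remote sites | Variance | Power |
|---|---|---|
| Steps 1 and 8 (worst, 1 of 28) | 0.00144 | 65.2% |
| Steps 1 and 2, or 7 and 8 | | 66.3% |
| One at an end, the other at step 4 or 5 | | 72.3% to 72.9% |
| Steps 4 and 5 (best) | 0.00111 | 77.6% |
| Mean of the 13 with an end step | | 70.0% |
| Mean of the 15 without an end step | | 75.1% (range 72.5% to 77.6%) |
| Mean of all 28 | | 72.8% |

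Worst order: 0.10/√0.00144 = 2.63, 2.63 − 2.241 = 0.39, Φ = 65%. The worst order is 72.8 − 65.2 = 7.6 points below the average order and 77.6 − 65.2 = 12.4 below the best.

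**Sensitivity of the best-to-worst gap.**
- Remote sites at 7 a month: 14.8 points (63.0% to 77.9%, before rounding). At 13 a month: 10.1 points (67.1% to 77.2%).
- Cluster autocorrelation 0.8: 11.0 points.
- 10 to 20 calendar months, categorical time: 10.4 to 15.4 points.
- Linear time: 5.7 points.
- No transition gap, 9 months: 1.5 points (92.2% to 93.7%).

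In all of these variants, steps 1 and 8 together are the worst placement.

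**The case against.** The strongest reply is that nothing here is wrong. Simple randomisation of the order is valid, the model has fixed time effects and a random facility effect, and the estimate is not biased. The article is also condensed: a computer-generated order could still have been a restricted one, with the detail in the full protocol. Both points stand. They make this an optional improvement, and if a restriction already exists, one added clause closes it.

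It is also fair that the gain is modest and model-dependent. The article does not say how time is coded, Fig. 1 is not reproduced in the text at hand, and the site volumes are assumed within the eligibility ranges. The no-transition layout that reproduces the stated power is almost insensitive to order. Against that, the article does specify a transition whose data are dropped, so the transition-excluded layout is the relevant one.

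Three stronger readings are tempting and are not supported:
- **That any first or last placement costs 12 points.** That is the best order against the worst, and the worst needs remote sites at both ends. One remote site at an end with the other at step 4 or 5 gives about the average power.
- **That site order explains the shortfall from over 90%.** Equal sites already give 74.2% once the transition is excluded, and no placement in the 11-month layout exceeds 77.6%.
- **That an unrestricted order confounds remoteness with calendar time in a way a restriction would cure.** With one site per step, every order ties each site to one crossover date.

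**Conclusion.** The point holds as a cheap design improvement. The article fixes two site-size groups and reports a random order without saying that the order takes account of them. Under the assumptions listed, there is a 46% chance of an order that costs about 5 points of power on average (70.0% against 75.1%). There is a 1 in 28 chance of one that costs about 8 points against the average order. The direction is the same in every variant tried. The size is not: it depends chiefly on categorical months and on excluding the transition data. The figures are normal approximations from a linear model, with no small-sample correction for eight clusters, so they serve better for comparing orders than as absolute power.

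**What to change.** Randomise all eight sites subject to neither remote hospital being at step 1 or step 8, and state this where Methods/design describes the order. In the base case, minimum power rises from 65.2% to 72.5% and mean power from 72.8% to 75.1%.

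A further rule that the two remote sites not be adjacent is optional, for spread over time only. It adds no power (mean 75.2% with it, 75.1% without) and rules out steps 4 and 5, the most precise placement.

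The cost is one line in the randomisation program, with no extra patients, sites or months. Admissible orders fall from 8! = 40,320 to 15 × 2! × 6! = 21,600, and any permutation test must draw from that restricted set. If the order has already been drawn, report it and recompute power for that order with the actual site volumes. The mismatch between the stated power and the excluded transition months needs its own correction.

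### Detected medication errors measure how hard the service searches, so they are a process measure and should not stand for error frequency or be costed as harm in the cost-benefit analysis

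*Protocol article*

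**What the plan says.** The protocol article mentions medication errors in five places.

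- **Background, aims.** The first aim is to "Investigate if the VCPS results in a detection of preventable medication harms, reductions of readmission, falls and length of stay". Detection is a wanted result here, set beside three outcomes that should fall.
- **Methods/design, Table 1.** The outcome rows include "Detection of preventable medication errors", taken from a facility-level Health Intelligence Unit (HIU) report. No other outcome row concerns medication errors.
- **Methods/design, outcomes paragraph, repeated in the Appendix table.** "Secondary outcome variables include 28-day readmission, hospital length of stay (LOS), number of falls and detection of medication-related errors". The model for routine data has fixed effects for time, period (pre or post) and patient confounders, and random effects for facility and patient.
- **Methods/design, economic analysis.** The cost-benefit analysis (CBA) will try to include outcomes "valued in monetary terms such as LOS, the cost of treating adverse events (falls, medication-related errors) and potentially preventable admissions". On inputs, it says: "Both analyses will rely on health care utilisation data outlined in Table 1".
- **Methods/design, intervention.** The virtual pharmacists reconcile and review medications, and "A summary of the Med Rec and any identified issues will be documented on the eMR Medication Management Plan".

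The study sites have no on-site pharmacist, and the Appendix records no masking.

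**The concern.** A count of detected errors is the product of two things: how many errors occur and what share of them is found. The VCPS is meant to lower the first and raises the second by its nature. Search effort changes at each site when exposure changes, so the pre/post term in the model carries both effects. Randomising the order of the steps protects against time trends. It does not protect against a change in ascertainment that is part of the exposure.

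Two readings are at stake. If the outcome is reported as an error rate, a real fall in errors can be hidden or reversed. If the same count is priced in the CBA, each additional detection becomes an additional adverse event charged to VCPS months. The benefit-cost ratio, which the protocol judges against 1, would then be too low.

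The wording adds to the difficulty. The thing counted is harms in the aims, preventable errors in Table 1 and medication-related errors in the outcomes paragraph.

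**Working it through.** The protocol gives no figure for detected errors, so there is nothing to reproduce. The check sets the passages side by side and then adds an illustration.

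**Direction.** Under the aims, a higher count is success. In the CBA, medication-related errors sit with falls as events that cost money to treat, so a lower number is success. These can be two different quantities (errors found, and adverse events treated), but Table 1 supplies a measure only for the first.

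**Illustration.** Let r be the true relative reduction in errors and D the ratio of detection in VCPS months to control months. Then

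detected ratio = D × (1 − r), and the count falls only if r > 1 − 1/D.

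Inputs from the sample size paragraph: baseline reconciliation 11%, target 11 + 10 = 21%, ratio 0.21/0.11 = 1.909. Assume that a share s of detection scales with reconciliation coverage:

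D = 1 + s × (1.909 − 1).

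The share s is an assumption, because the document gives no value. It is 0 if nothing the pharmacist finds reaches the HIU report.

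| s | D | Change in count, no true change | True reduction needed before the count falls | Change in count if true errors fall 20% |
|---|---|---|---|---|
| 0 | 1.000 | 0% | 0% | −20% |
| 0.25 | 1.227 | +23% | 18.5% | −2% |
| 0.5 | 1.455 | +45% | 31% | +16% |
| 1 | 1.909 | +91% | 47.6% | +53% |

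The last row is not an upper bound, because the service also includes clinical medication review, which adds search beyond reconciliation.

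**Effect on the CBA, if the detected count is used.** Take 100 detected errors in control months, a unit treatment cost c, a true 20% reduction and s = 0.5. With detection held at the control level, the benefit term is c × (100 − 80) = +20c. With the detected count it is c × (100 − 116) = −16c. A saving would be recorded as a loss.

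**The case against.** The strongest objection is that the outcome is named as detection wherever it appears, and that the first aim already makes more detection the favourable result. A reader might infer that a better service will look harmful on this secondary outcome. The document does not support that: read as named, a rise is success. This part of the objection stands, and the problem arises only if the count is interpreted as error frequency or priced as harm.

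Second, a reader might infer that the CBA will certainly charge detections to the VCPS. The text does not say so. What it costs is the treatment of adverse events, and the sentence pointing to Table 1 goes on to describe resource use such as pharmacist time, education and system changes. An intercepted error that needed no treatment would add nothing under that wording. This also stands: the link is an inference from there being no other error outcome in Table 1.

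Third, pharmacists record what they find in the Medication Management Plan and in the clinical pharmacy intervention records, which Table 1 already lists under process measures. The error outcome comes from a different source, the HIU report. The document does not say whether one feeds the other, so the size of any artefact is unknown and may be nil.

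Fourth, operational definitions and costing rules commonly sit in the full protocol or an economic plan, so their absence from the article is no finding. That is right. But the article itself classes detection as an outcome rather than a process measure, and it names medication-related errors as a costed adverse event. Those are choices it has made.

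A reader might also infer that the trial means to prove from this outcome that pharmacists reduce errors. The abstract and Discussion present that as existing knowledge, so the point does not rest on it.

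**Conclusion.** The concern holds in a limited form. Detected errors depend on search effort, which the VCPS raises, so a pre/post difference shows a change in detection and cannot show a change in the frequency of errors or harm. If the detection count also feeds the CBA, the benefit-cost ratio is biased against the service. That condition is inferred, not stated.

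The size cannot be established from the document. On the protocol's own reconciliation target, the artefact runs from none (s = 0) to a 91% rise with no true change (s = 1), and s is wholly assumed. The co-primary outcomes are unaffected, as is the cost-effectiveness analysis, which uses 28-day readmission. This is a point about one secondary outcome and one CBA input, worth settling before analysis because the change is cheap.

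**What to change.** 1. Move detection of medication errors to the process measures in Table 1, state that an increase is expected, use one definition throughout, and say that it will not be interpreted as an error rate.
2. In the CBA, count only medication errors that reached the patient and required treatment. Take them from the same routine source, by the same rule, in control and VCPS months.
3. Do not exclude incidents reported by the virtual pharmacist from the base case. That exclusion can remove events only in VCPS months and would tilt the result towards the service. At most, show results with and without them as a sensitivity analysis.
4. If treated errors cannot be separated from detected ones, leave medication-related errors out of the base-case benefit-cost ratio and report them descriptively.

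The routine source needs to be named. The article mentions the incident management system only for harms arising from the VCPS, so it cannot be assumed to cover control months in the same way.

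The cost is some rewording of Table 1, the outcome list and the CBA paragraph, plus a filter on routine data. The downside is fewer countable events and a less precise error component.
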